4. ESTIMATED DURATION OF THE STUDY

Five years (2010–2015)

5. SPECIFIC AIMS

This project builds upon [name] earlier study, “Safer Sex Intervention for Female Sex Workers in Mexico” (Project #051182). In that study, we developed a brief behavioral intervention to promote condom use and enhance safer-sex negotiation skills among FSWs in Mexican border cities. The intervention (named *Mujer Segura* in Spanish) was recently demonstrated to be efficacious, mediated by improvements in FSW self-efficacy (see “Progress Report”).

As a result, the federal government in Mexico expressed interest in scaling up the intervention across Mexico and encouraged us to conduct a formal evaluation of the implementation process in order to learn how most effectively to implement this type of intervention throughout Mexico. Therefore, we propose to test a train-the-trainer model for transporting *Mujer Segura* into existing Community Based Organizations (CBOs) in Mexico. This model seeks to develop local and culturally relevant expertise and infrastructure to further disseminate and maintain *Mujer Segura* within each CBO. We will examine whether this model can develop a network of HIV/STI prevention services for FSWs with self-sustaining levels of model fidelity and provider competency. Levels of fidelity to the intervention protocol as well as the efficacy of the intervention itself will be measured at each stage to see how well fidelity and efficacy are preserved through the process.

Our specific aims and corresponding hypotheses are as follows:

Aim 1: To determine if the train-the-trainer implementation model can achieve and sustain high levels of intervention model competency and fidelity.

Hypothesis 1. Competency and fidelity as measured by direct observation methods and FSWs’ reports will achieve at least 90%.

Aim 2: To characterize the relationship between individual provider characteristics and organizational factors, and their impact on the implementation of our intervention, using a mixed-methods (quantitative/qualitative) approach.

Hypotheses 2a –2f: Specific quantitative hypotheses to be examined include:

2a) More positive organizational culture and climate will be associated with more positive attitudes toward evidence-based interventions (EBI).

2b) Personal dispositional innovativeness will mediate the relationship between staff demographics and attitudes toward EBI. Specifically, staff demographics (i.e., higher education level, shorter job tenure) will be associated with higher personal dispositional innovativeness, and personal dispositional innovativeness will be positively associated with attitudes toward EBI.

2c) Social networks indicating more connectivity and positive information regarding *Mujer Segura* will be positively associated with attitudes toward EBI.

2d) Attitudes toward EBI will meditate the relationship between personal dispositional innovativeness and implementation fidelity. Specifically, personal dispositional innovativeness will be positively associated with attitudes toward EBI, and attitudes toward EBI will be positively associated with implementation fidelity.

2e) More positive attitudes toward EBI will be associated with greater implementation fidelity.

2f) Greater fidelity will be associated with more positive FSW outcomes.

Aim 3: To determine whether the implementation of *Mujer Segura* by each CBO is associated with decreased sexual risk behaviors among Mexican FSWs over a six-month period (e.g., increased condom use with clients, reductions in STI incidence);

Hypothesis 3. As in the completed efficacy study, FSWs randomly assigned to the theory-based *Mujer Segura* intervention condition will show greater reductions in high risk sexual behavior with clients (i.e., fewer unprotected vaginal and anal sex acts, lower global STI incidence) at six-month follow-up as compared to FSWs who receive standard counseling.

Aim 4: To determine whether improvements in FSWs’ sexual risk behaviors are associated with variations in intervention fidelity and counselor competency.

Hypothesis 4. Among FSWs in the *Mujer Segura* condition, improvements in sexual behavior with clients at six-month follow-up (i.e., frequency of unprotected vaginal and anal sex, STI incidence) will be associated with higher levels of counselor competency and fidelity to the implementation model.

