To avoid contamination between the experimental and comparison conditions, CBO staff will first evaluate and deliver the “usual care” counseling session to the control group before learning how to deliver the experimental counseling intervention. A total of 80 FSWs will be recruited at each site, of whom 40 will be randomly assigned to the *Mujer Segura* counseling condition and 40 will be assigned to the usual care risk-reduction counseling condition, which was developed by Mexico’s federal HIV-AIDS agency (CENSIDA) and focuses upon basic educational information, personal risk assessment, and strategies for reducing personal risk. Participants who are randomized at intake to the experimental condition will be asked to return at a later date to receive their assessment and intervention.

Phase Two: Training the CBO’s designated “internal trainer.” Once the comparison condition FSWs have been assessed and counseled, a participating CBO staff member will be designated as the CBO’s “internal trainer” and receive intensive training in both the *Mujer Segura* protocol and in effective methods for teaching the protocol to other staff. Drs. [name], [name], and [name] and two practice experts from the Ciudad Juarez training center will conduct an intensive, eight-day training.

Phase Three: The “internal trainer” trains CBO staff who in turn deliver the *Mujer Segura* intervention. The practice experts will remain at the CBO for two weeks to observe and coach the internal trainer as she trains the counselors who will deliver *Mujer Segura* to the 40 randomized FSWs, and the counselors will begin to deliver the intervention. The experts will give feedback on the delivery and help the CBO counselors resolve challenging or idiosyncratic case issues or presentations. After the practice experts leave, they will maintain weekly telephone and email contact with the CBO counselors.

While the CBO is implementing *Mujer Segura* (over approximately a six-month period), the ethnographers will return periodically to monitor intervention fidelity. Finally, at the end of implementation, the ethnographers will return to repeat the staff qualitative interviews and focus groups that were performed at the outset, in order to enable the researchers to see if any changes have occurred in staff attitudes or organizational characteristics over the course of implementing the intervention.

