Phase Four: Maintenance. In the fourth and final phase of the implementation model, the internal trainer will shift roles to maintenance. Maintenance activities include training and coaching new hires, a lower level of in vivo coaching and fidelity monitoring of existing trainees (quarterly rather than weekly or bi-weekly), and planning any major adaptations or evolutionary modifications of the model.

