***Data Analysis and Interpretation***

Aim 1: Equivalence testing will be used to evaluate Aim 1 using Schuirmann’s (1987) test of equivalence. A nominal alpha of .05 will be used in the proposed analysis. Given the nested data structure (i.e., service providers nested in CBOs), hierarchical linear modeling will be used to adjust standard errors for possible dependency among observations. The outcome of interest in Aim 1 focuses on *Mujer Segura* fidelity. We expect that service providers will attain approximately 90% treatment fidelity when considering that 100% is perfect fidelity.

Power calculations for equivalence tests proposed for Aim 1 were conducted using SAS® Proc Power. Using the bounds and nominal alpha specified above, along with a hypothesized difference between population group means of zero and a standard deviation of 15 in each group, the proposed sample size of 120 (10 staff x 12 CBOs) would yield power of >.89 to reject the null hypothesis of mean differences in favor of the alternative of group equivalence. This power calculation is based on the assumption that observations are independent. If the observations are dependent, this will be an overestimate of statistical power. One method of calculating power in this case is to estimate the degree to which the variance will be increased due to non-independence. Specifically, the variance will be increased by a factor of 1+(m-1)*ICC, also known as the design effect, where m is the average cluster size and ICC is the intraclass correlation coefficient. While we don’t have prior ICCs for *Mujer Segura* fidelity ratings, in our work examining service provider attitudes toward EBI implementation in CBOs, ICCs were generally low. However, in a larger and more representative study of CBOs across the U.S., the ICC was .03, and we expect the fidelity ICC to be of similar magnitude. Using the average ICC of .03 from this recent study, and an average cluster size of 8, the variance is estimated to be increased by a factor of 1.21. Given a total sample size of 96, the functional sample size would be 79.34 (i.e., total sample size/design effect), which would yield power of .80.

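### Aim 1 asks whether fidelity is achieved and sustained, but the stated Aim 1 test has no time or stage term, so it cannot support the claim that fidelity is sustained

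*Protocol*

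**What the plan says.** Protocol Section 5 (Specific Aims) puts two questions in Aim 1: whether the model "can achieve and sustain high levels of intervention model competency and fidelity". The same section says that fidelity and efficacy "will be measured at each stage to see how well fidelity and efficacy are preserved through the process". Hypothesis 1 sets only a level: "Competency and fidelity as measured by direct observation methods and FSWs’ reports will achieve at least 90" per cent.

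Section 8 (The Implementation Process: Organizational Level) describes measurement over time. In Phase Three the practice experts stay on site for two weeks and afterwards keep weekly contact by phone and email. Over about six months of delivery, "the ethnographers will return periodically to monitor intervention fidelity". In Phase Four (Maintenance) the internal trainer's duties include "fidelity monitoring of existing trainees (quarterly rather than weekly or bi-weekly").

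Section 8 (Data Analysis and Interpretation) gives the Aim 1 analysis. "Equivalence testing will be used to evaluate Aim 1 using Schuirmann’s (1987) test of equivalence". "Given the nested data structure (i.e., service providers nested in CBOs), hierarchical linear modeling will be used" to adjust the standard errors. The expected result is a level: "We expect that service providers will attain approximately 90% treatment fidelity when considering that 100% is perfect fidelity". The power statement assumes no true difference between group means and an SD of 15 in each group. It counts 120 staff (10 × 12 CBOs), then 96 staff with a cluster size of 8, a design effect of 1.21 and a functional sample size of 79.34. The groups are not defined. The equivalence bounds are said to be given earlier, but no figure for them appears.

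**The concern.** Sustainment is central to a train-the-trainer design: outside support is heaviest at the start and is then withdrawn. The period that tests the model is the one after the experts leave, and the stated analysis does not separate it from the coached period. A mean over both can meet the target when early fidelity is high and later fidelity is lower.

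The result is meant to inform a national scale-up (Section 5). If the Aim 1 test is passed and reported as an answer to Aim 1 as worded, readers will take it as evidence that fidelity lasts, which the test did not examine. The ratings needed to examine it are planned, at least within Phase Three, but the stated analysis makes no use of their timing.

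**Working it through.** **1. What the Aim 1 sizing implies.** Inputs from the Aim 1 text: intraclass correlation .03, average cluster size 8, total 96, SD 15, true difference 0, alpha .05.

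- Design effect = 1 + (8 − 1) × .03 = 1.21, as stated.
- Functional n = 96 / 1.21 = 79.34, as stated.
- The stated power of .80 can be matched only by solving back for the bounds. An exact-t two one-sided test at .05 per side gives .806 at n 79.34, with bounds of ±5 for a single mean or ±10 for two equal groups sharing the total.

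The count of 96 is 8 × 12, that is, people, and the cluster of 8 is providers per CBO. With k ratings per provider there would be 96k ratings in clusters of 8k. The figures therefore fit one value per provider. This is an inference, because the text does not say it.

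**2. Is time handled elsewhere?** Aim 2 uses fidelity in correlations and mediation tests, not as a trend. The model for Aims 3 and 4 does name time and its interaction with intervention condition, but for the sex workers' outcomes. No passage gives an analysis of fidelity over time.

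**3. What a pooled mean can hide.** Suppose fidelity is 96% while coached and 84% afterwards (assumed values), and let w be the share of ratings from the coached period. The pooled mean is 96w + 84(1 − w) = 84 + 12w.

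- w = .5: 84 + 6 = 90%, the same as a constant 90%.
- Ratings spread evenly over 26 weeks, two of them coached: (2 × 96 + 24 × 84) / 26 = 2208 / 26 = 84.9%.
- With the same even spread, a pooled mean of 90% needs (26 × 90 − 2 × 96) / 24 = 89.5% after coaching.

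How much is hidden depends on when the ratings are taken, and the protocol does not fix that. Ratings concentrated early hide more.

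**4. Could a fall be detected?** The protocol has no figure for this, so what follows is illustrative. Assume an early and a late score on every counselor, SD 15 each, within-provider correlation r, functional n 79.34, two-sided .05 and a normal approximation.

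- SD of change = 15 × √(2(1 − r))
- SE = SD of change / √79.34, where √79.34 = 8.907
- Power = Φ(fall / SE − 1.96)

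| r | SD of change | SE | Power, 5-point fall | Power, 3-point fall |
|---|---|---|---|---|
| .3 | 17.75 | 1.99 | .709 | .325 |
| .5 | 15.00 | 1.68 | .844 | .429 |
| .7 | 11.62 | 1.30 | .969 | .633 |

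The 95% interval for the change has a half-width of 1.96 × SE, about 3.9 points at r = .3 and 2.6 points at r = .7.

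**The case against.** The best case for the protocol has four parts.

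- **The analysis matches Hypothesis 1.** The hypothesis names only a level, and a list of model covariates may be left to a statistical analysis plan, which is not at hand. The first half is true. However, the protocol itself fixes the test, the nesting and the sample size for Aim 1, and these do not cover the aim as worded.
- **The groups are undefined.** The power statement speaks of a difference between group means. If the groups were stages, the test would bear directly on sustainment. The text does not rule this out, but nothing in it says so, and the nesting names providers and CBOs only. The ambiguity is a further reason to state the contrast.
- **A decline would not simply go unseen.** A reader might infer that any decline would be missed. The documents do not support that: a large fall lowers the mean, as the 84.9% case shows, and the planned monitoring could reveal a fall descriptively. What stands is that a decline could pass the formal test if the average stays within the bounds.
- **Maintenance ratings may not be study data.** Phase Four monitoring is described as an activity of the CBO's internal trainer, and the last research visit described is at the end of implementation. This stands. It limits the remedy to Phase Three unless Phase Four ratings are collected for the study.

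**Conclusion.** The mismatch is real. Aim 1 asks about achieving and sustaining fidelity, while the stated analysis addresses a level at most. Passing it would not support a claim that fidelity is sustained. This should be changed, and the change is cheap.

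Some matters remain open. One value per provider is inferred from the sample size and cluster size. The size of any masking cannot be fixed from the protocol: with the assumed 96% and 84%, the pooled mean runs from 84.9% under evenly spread ratings to 90% under equal weighting.

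It would also be too strong to say that the planned data will certainly show a decline. Under the assumptions above, power is reasonable to high for a 5-point fall (.709 to .969) and low to moderate for a 3-point fall (.325 to .633). These figures assume both scores on every counselor. They also carry over to change scores a design effect that the protocol derives for a mean level, with an intraclass correlation taken from another study. A non-significant time effect would therefore not in itself show that fidelity was sustained, so the interval is needed.

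**What to change.** Amend the Aim 1 analysis as follows.

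- Model the repeated Phase Three fidelity ratings at three levels (ratings within providers within CBOs), with a fixed effect for time since training or for stage (coached versus after the experts leave). Date every rating. If few ratings fall in the coached weeks, use time rather than the two-stage contrast.
- Apply the 90% criterion at the last monitored stage as well as the first, and report the change with its confidence interval.
- Define the comparison groups and print the equivalence bounds, so that it is clear which contrast is tested.
- Include Phase Four ratings only if they are collected as study data. Otherwise limit the conclusion on sustainment to the implementation period.

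The cost is revised wording and modest extra modelling of ratings already planned for Phase Three. The downside is that the last stage may have fewer ratings and so a wider interval. Extending the conclusion to maintenance would need Phase Four ratings to be study data, which may mean added data collection.

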6. BACKGROUND AND SIGNIFICANCE

Our research with FSWs suggests that HIV prevalence is rising rapidly among FSWs on the Mexico-U.S. border. In a sample of 415 FSWs in Tijuana in 1991, HIV prevalence was 0.5%, but in our more recent study of 924 FSWs in both Tijuana (bordering San Diego, CA) and Ciudad Juarez (bordering El Paso, TX), HIV prevalence was 6%, and HIV incidence in the control group of our subsequent intervention study was 2 per 100 person-years (py). In the same study, prevalence of gonorrhea, Chlamydia and active syphilis was 6.4%,13% and 14.2%, respectively (see [name] et al. in Bibliography).

As described above in Specific Aims, our *Mujer Segura* brief behavioral intervention proved efficacious in lowering sexual risk behavior and the incidence of HIV and STIs relative to FSWs who received a standard, time-equivalent didactic counseling session. As a result, the federal government in Mexico has expressed interest in scaling up the intervention across Mexico and encouraged us to conduct a formal evaluation of the implementation process in order to learn how more effectively to implement this type of intervention throughout Mexico.

Several meta-analytic reviews have identified efficacious interventions for reducing high-risk sexual behaviors in a variety of populations, including Men who have Sex with Men (MSM), ethnic minorities, and HIV+ individuals. However, there has been a lack of empirical study of the implementation of evidence-based HIV interventions (EBIs) to community-based organizations (CBOs). To encourage the adoption of EBIs by CBOs, the Centers for Disease Control (CDC) in 2002 implemented the Diffusion of Effective Interventions (DEBI) Project, which was designed to implement evidence-based interventions in community-based programs. The experiences of DEBI participants form the basis for our understanding of key issues relevant to translating research into practice.

Both client and provider characteristics are important in terms of achieving a good fit between the EBI and the implementation agency. *Mujer Segura* is a brief (35-minute) intervention that meets the needs of FSWs in Mexico. Because this is a resource-poor population, FSWs will not accept a program that involves a major time commitment that would interfere with income earning. *Mujer Segura* also offers clients free HIV and STI testing, which is valued by the participants. FSWs are a diverse group in terms of age and years of work experience; thus, women are at different stages in the behavioral change process, which is taken into account in the protocol (stages of change theory is incorporated into the motivational interviewing component). Also, the one-on-one counseling element is appealing to FSWs because many are not willing to participate in group sessions. *Mujer Segura* is also a good fit with the CBOs that are willing to adopt this intervention. “Values–innovation fit” is defined as the fit between the values an organization or service provider implementing an innovation and the characteristics of the innovation itself and is important in the implementation of innovations such as *Mujer Segura*. Data gathered from the directors of the MEXFAM CBOs indicate that *Mujer Segura* is compatible with MexFam’s philosophy and mission. The intervention was also perceived as feasible, relevant to local culture, sustainable, and able to fill a gap in existing HIV prevention services for FSWs in resource-constrained settings (see below, Preliminary Studies).

7. PROGRESS REPORT/PRELIMINARY STUDIES

***Mujer Segura Intervention Trial Results***

Results of the first phase of *Mujer Segura* (NIH R01 MH065849, Project #051182) were described in the following article (see Appendix 1):

[name], T.L., Mausbach, B.T., Lozada, R., [name], H., [name], S.J., Fraga, M., Orozovich, P., Abramovitz, D., de la Torre, A., Amaro, H., Martinez, G., Magis-Rodríguez, C., and [name], S.A. Efficacy of a brief behavioral intervention to promote condom use among female sex workers in two Mexican-u.s. border cities. *American Journal of Public Health.* 98 (11): 2051-7, 2008.

After participating in our 35-minute theory-based intervention, FSWs randomized into *Mujer Segura* had a 40% decline in cumulative STI incidence (p=0.03). Incidence density for the intervention vs. control was 13.8 vs. 24.92 per 100 person-years (py) for STIs combined (p=0.03), and 0 vs. 2.01 per 100 py for HIV (p<0.001), with concomitant increases in total numbers and percentages of protected sex acts and decreases in total numbers of unprotected sex acts with clients (p<0.05) at six-month follow-up. These results establish a baseline for efficacy against which successive implementations of *Mujer Segura* at other sites within Mexico can be measured.

Our human-subjects experience with *Mujer Segura* was excellent. A total of 1,853 participants were recruited, and none complained about any aspect of her treatment. Participant confidentiality was effectively maintained throughout the study. This was due to thorough training of staff at all implementation sites on the importance of informed consent and participant confidentiality. The same training measures will be implemented in the present study at all implementation sites.

***Selection of CBOs at which to Study the Implementation of the Intervention***

With the assistance of [name], a consultant on this project and Director of CENSIDA (the Mexican federal agency for the control and prevention of HIV and AIDS), we identified a community-based, non-profit organization that is both willing and able to provide the facilities and staff that we require in order to implement our study. MexFam has a total of 20 CBOs in 19 Mexican states. We excluded eight clinics from further consideration based on the following criteria: based in a rural community, clinic population does not include FSWs, clinic program is focused on children under the age of 18, or clinic is based in a city that participated in the original *Mujer Segura* project. Based on these exclusion criteria, 12 MexFam CBOs in 12 cities in Mexico were evaluated and determined to possess the qualities considered optimal for participation (see list in Section 3, above).

Each CBO selected for participation has been deemed to have the following characteristics: 1) a core of eight high-potential, stable staff members who will be trained as *Mujer Segura* counselors; 2) an organizational culture that supports innovation and evidence-based perspectives; 3) strong local reputation and street credibility; 4) capacity to deliver professional peer-to-peer training; 5) strong cultural competency and knowledge about FSW populations.

